## Abstract

**Background:**

Heart failure is a major cause of mortality and morbidity. As mortality rates are high, it is important that patients seen by general practitioners with symptoms suggestive of heart failure are identified quickly and treated appropriately. Identifying patients with heart failure or deciding which patients need further tests is a challenge. All patients with suspected heart failure should be diagnosed using objective tests such as echocardiography, but it is expensive, often delayed, and limited by the significant skill shortage of trained echocardiographers. Alternative approaches for diagnosing heart failure are currently limited. Clinical decision tools that combine clinical signs, symptoms or patient characteristics are designed to be used to support clinical decision-making and validated according to strict methodological procedures. The REFER Study aims to determine the accuracy and cost-effectiveness of our previously derived novel, simple clinical decision rule, a natriuretic peptide assay, or their combination, in the triage for referral for echocardiography of symptomatic adult patients who present in general practice with symptoms suggestive of heart failure.

**Methods/design:**

This is a prospective, Phase II observational, diagnostic validation study of a clinical decision rule, natriuretic peptides or their combination, for diagnosing heart failure in primary care. Consecutive adult primary care patients 55 years of age or over presenting to their general practitioner with a chief complaint of recent new onset shortness of breath, lethargy or peripheral ankle oedema of over 48 hours duration, with no obvious recurrent, acute or self-limiting cause will be enrolled. Our reference standard is based upon a three step expert specialist consensus using echocardiography and clinical variables and tests.

**Discussion:**

Our clinical decision rule offers a potential solution to the diagnostic challenge of providing a timely and accurate diagnosis of heart failure in primary care. Study results will provide an evidence-base from which to develop heart failure care pathway recommendations and may be useful in standardising care. If demonstrated to be effective, the clinical decision rule will be of interest to researchers, policy makers and general practitioners worldwide.

**Trial registration:**

ISRCTN17635379

## Background

Heart failure (HF) is a life-threatening, costly condition [1]. It affects at least 2.3% of adults over 45, rising to 4% in over 75 year olds [2]. HF markedly reduces quality and length of life [3], and treatment costs are high, second only to stroke and mainly due to high admission rates [4]; estimated to consume almost 2% (£751 million) of total NHS expenditure [5]. HF is a diagnostic challenge, as symptoms are non-specific and physical signs can be subtle [6-9]. Because outcomes in HF are linked to stage of disease and evidence-based treatments alter natural history as well as improve symptoms and prognosis [10-12], accurate early diagnosis and treatment is essential to reduce morbidity and mortality. As most patients with suspected HF are seen initially by GPs [6,13], the need for early and accurate diagnosis in primary care is essential to ensure optimum management and appropriate treatment is initiated rapidly.

Specialist review of symptoms and signs plus objective investigations, including echocardiography (Echo), is the established ‘gold standard’ for diagnosing left ventricular systolic dysfunction (LVSD) and increasingly suspected HF with a preserved ejection fraction (HFpEF) [14]. Diagnosing HF requires objective estimation of cardiac function (i.e. Echo) since determining the aetiology and stage of HF leads to different management choices such as initiation of angiotensin-converting enzyme (ACE) inhibitors [10], ß-blockers [11] and aldosterone antagonists in most patients with LVSD [15], cardiac resynchronization therapy for those with LVSD and broad QRS complex [1], or surgery where significant valve disease exists. These therapies improve symptoms, prognosis and quality of life, and can reduce healthcare utilisation and NHS costs. However, a difficulty is that performing Echo on all suspected HF patients would be costly as many patients are found not to have HF.

Diagnostic strategies can vary between GPs if a case of HF is suspected, but the most appropriate strategy is unclear. These include an initial clinical assessment of patient signs and symptoms using physical examination, and investigations such as lab blood tests or chest x-ray. Additionally, screening tests, such as electrocardiogram (ECG) and natriuretic peptide (NP) tests, where available, have been recommended by NICE as potential ‘rule out’ tests for HF to limit unnecessary referrals to echocardiography [16,17]. Routine clinical assessment takes place over multiple consultations, due mainly to diagnostic uncertainty and delays that occur in the referral pathway.

Diagnostic uncertainty in clinical practice, difficulties diagnosing HF and local organisational factors such as limited availability of diagnostic services, or delays inherent in the current referral system, create barriers to the early and accurate diagnosis of HF. Access to Echo is variable, often delayed, and limited by the significant skill shortage of trained Echocardiographers [14,16,18,19]. As a consequence, many GPs rely solely on, often inaccurate, unstructured clinical assessment [7,8,18,20]. However, diagnosing HF on clinical grounds alone can be unreliable due to difficulty in interpreting signs [21] and differences between doctors in obtaining symptoms and signs [13,22]. Many GPs order a chest x-ray, or arrange an ECG [7]. However, although a normal ECG will exclude LVSD in most cases, changes may be subtle and lack of GP interpretation skills may still require referral for specialist opinion. A normal chest x-ray does not exclude HF [23]. A key dilemma facing GPs is deciding which patients to refer for Echo and when; and lack of a systematic method for guiding the diagnosis of HF presents a further obstacle [7], adding to cost and delay. Diagnostic uncertainty or inaccurate diagnosis can result in diagnosis being delayed until HF symptoms are more obvious and therefore more severe, multiple GP consultations and hospital admissions, or people are treated incorrectly.

A growing body of evidence suggests the potential utility of B-type natriuretic peptides (NPs), namely BNP or NT-proBNP, both released from myocardium in response to wall stretch, as diagnostic cardiac biomarkers of HF. These NP tests provide an exciting opportunity to support the clinical assessment of symptomatic primary care patients, as normal levels can rule out HF given the high sensitivity of these tests (98%) [24], but confirmatory Echo is needed in patients with elevated peptides to confirm the diagnosis [24-28].

There is uncertainty about the best cut-off levels of NPs in primary care and the cost-effectiveness/benefit has not been established. NP testing is under-used because reliable data on BNP and NT-proBNP performance in the diagnosis of HF are limited mainly to epidemiological sub-studies or to prospective validation in emergency department settings [27,29-31], with limited data on test performance within symptomatic patients routinely presenting in primary care [24,28,32]. Best assay cut-offs have therefore been largely imputed and assay performance against or with ECG and symptom score unclear. Moreover, obesity and certain HF medications can lower peptide levels and elevated levels can be associated with unrelated conditions and other factors such as increased age, gender and renal insufficiency [25]. These factors therefore impair the utility of NPs as a diagnostic marker of HF if used alone. The addition of a B-type NP test to the current diagnostic pathway, with specialist referral if test results are abnormal, is a suggested alternative approach that may be superior and cost-effective [33]. However, the cost-effectiveness of NPs versus standard diagnostic triage is not established.

Current consensus suggests a superior approach would be to combine NP testing with standard clinical assessment. In a recent prospective, randomised controlled trial of 305 elderly patients with symptoms of recent onset breathlessness or oedema GP diagnoses were more accurate with NT-proBNP test results in addition to routine clinical assessment than without, mainly due to the ability to correctly rule out HF [28]. A recent meta-analysis concluded that the use of NPs could help reduce the demand for Echo and cardiology referrals [34]. However, determining the optimal manner in which to combine clinical features from clinical assessment and diagnostic tests, including NP tests, remains extraordinarily challenging.

Clinical decision rules (CDRs) are evidence-based clinical tools designed to be used to help clinician decision-making in a standardised and cost-effective manner, and are developed according to strict methodological procedure [35,36]. These clinical tools are based on a parsimonious set of variables that can quantify the contribution from history, physical examination and diagnostic tests. They are developed and evaluated in three distinct stages prior to implementation into a clinical setting: 1) creation of the rule, establishing the independent and combined effect of explanatory variables such as symptoms, signs or diagnostic tests; 2) validation of the rule, establishing the accuracy and reliability of the tool in a separate population; and 3) impact analysis of the rule, establishing impact of applying the rule on patient outcome or health professional behaviour.

A number of CDRs have been developed to diagnose HF, using combinations of signs, symptoms and tests [37-39]. However, a major problem with all the studies is spectrum and referral bias since most were based on observational screening studies rather than symptomatic presenting patients and some were hospital rather than community based. Additionally, the tools are impractical outside a research or emergency department setting as they are based on a substantial number of variables; others rely on clinical signs where there is considerable inter-observer variation, even amongst specialists; and others rely on chest x-ray parameters, which would be difficult to apply in general practice.

Our recent NIHR HTA funded systematic review and independent patient data and meta-analysis [40,41] addressed this issue. We found individual symptoms (such as breathlessness and fluid retention) and signs (such as resting tachycardia and raised jugular venous pressure) are generally weak predictors of HF. Both ECG and BNP have high sensitivity for HF and are good tests at ruling out the diagnosis but BNP is more accurate than ECG. We found BNP and NT-proBNP to be of similar accuracy.

Our systematic review [40] identified one unpublished study which had developed a decision tool based on simple clinical features [42]. In our individual patient data analysis [40,41] we further developed this tool and validated it on other primary care data sets. We found that a simplified model, based upon simple clinical features (Male gender, history of myocardial Infarction, basal Crepitations, oEdema: ‘MICE’) and BNP derived from one data set, was found to have good validity when applied to other data sets, with the area under the curve between 0.84 and 0.96, and reasonable calibration. A model substituting ECG for BNP was less predictive. Our systematic review concluded that BNP could substitute for ECG for determining referral to Echo and some patients could be referred with no prior tests on the basis of clinical features alone.

We shall establish the clinical utility of B-type NP tests in informing the diagnosis of diastolic HF as well as LVSD and valve disease. Additionally, we shall determine the probability thresholds of the CDR above which Echo would be the most cost-effective diagnostic strategy, taking into account patient quality of life and survival. The results will contribute to scientific progress by solving the problem wherein GPs have clinical uncertainty about whether an Echo should be done or not for a patient whom they suspect may have HF. There is now an opportunity to provide these data and to potentially demonstrate that the CDR can improve patient management concerning diagnostic accuracy, clinical decision-making and cost-effectiveness.

Our study will build upon the current evidence and address the weaknesses in previous work. We have validated the CDR on primary care data sets but further validation in a symptomatic population in the real-life clinical setting is now indicated. Further exploration of the optimal NP cut-offs and further modelling of cost-effectiveness is also needed. We aim to prospectively validate the CDR in this study but GPs will not apply the CDR (applying the rule would be appropriate in an implementation study); GPs will refer all patients suspected of having HF and not previously diagnosed with Echo and we shall collect data on how well the CDR predicts the diagnosis of HF. The CDR’s impact potential will be demonstrated by evaluating whether its sensitivity and specificity is superior to that of GPs’ (unaided) decisions. Given the risk of delayed diagnosis of HF, GPs do not have clear guidance on whom to refer for further evaluation. Improving the ability of GPs to appropriately identify patients suspected of having HF is crucial not only to avoid unnecessary hospital admissions and reduce patient burden, but also to improve the quality of care for patients presenting to primary care with suspected HF.

We propose the following objectives:

1. To prospectively validate the performance of the CDR and compare it to using a natriuretic peptide assay alone on the diagnostic accuracy of HF in primary care

2. To determine if the CDR, or natriuretic peptide assay can be used in routine clinical practice to establish referral on for echocardiography in patients presenting with symptoms suggestive of HF

3. To quantify the most reliable cut-off levels of the natriuretic peptide assay in a group of symptomatic presenting patients

4. To model the cost-effectiveness of using the CDR in primary care

## Methods/design

### Study design and setting

REFER is a prospective, observational, diagnostic validation study of a CDR, natriuretic peptide or their combination, for diagnosing heart failure in primary care. The study will be conducted in 30 urban and rural primary care practices in Birmingham, West Midlands, England.

### Study population

All adult primary care patients aged 55 years or over presenting to their GP with recent new onset symptoms of breathlessness, lethargy or ankle oedema of over 48 hours duration, with no obvious recurrent, acute or self-limiting cause will be enrolled.

### Patient eligibility

Patient eligibility will be determined by the GP using information from clinical history and examination and recording clinical judgment via a GP web-based database. The eligibility criteria will be confirmed by investigation and specialist interpretation of clinical assessments. Objective evidence of HF (reference standard) will be determined by a specialist panel that will validate previous diagnosis and investigations.

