### Exclusion criteria

Patients will be excluded if any of the following criteria are met:

• Known pre-existing HF or LVSD of any cause. However, patients with a pre-existing label of HF but without objective evidence (i.e. echocardiography) of this will not be excluded

• Severe symptoms requiring urgent assessment or stabilisation (e.g. breathless at rest, hypotension, confusion)

• Obvious clinically determined alternative diagnoses such as chest infection, exacerbation of chronic obstructive pulmonary disease or asthma

• Recent acute coronary syndrome (within 60 days)

• Major co-morbidity or other alternative diagnoses of no obvious acute and self-limiting cause (e.g. malignancy, severe respiratory disease, renal dialysis, mental health problem)

• Unable to provide informed consent

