### Referral of patients to research assessment clinics

GPs will refer all eligible patients who have given verbal consent to participate in the study to one of our two research assessment clinics in two ways by: 1) asking the patient to telephone our research team administrator to arrange an appointment within seven days of the initial GP consultation, or the GP obtains patient contact details for entry onto the GP electronic database and the study team telephones the patient; and 2) GP completion of eligibility criteria onto the web-based Case Report Form will act as a referral letter, which we shall check to confirm eligibility and to ensure that the patient has contacted the research assessment team. If a patient changes their mind between agreeing to participate at the GP consultation and before attending their appointment at the research clinic, they are advised that they can cancel by telephoning either the research team or their GP. The patient can then re-consult with their GP, if necessary. Patients who decline to take part in the study will be managed as usual practice by GPs. When eligible patients decline to participate in the study or patients do not meet entry criteria for the study, GPs will complete a weekly electronic notification form of these details. These data will be used to assess potential selection bias.

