### Blood collection and biomarker assessment

We shall collect a 30ml blood sample by venepuncture into EDTA K2 blood tubes to perform a point of care NT-proBNP test using a Cobas h 232 Reader and Roche Diagnostics CARDIAC proBNP test strips, for immediate results, and to perform a serum creatinine test to exclude renal dysfunction and calculate an eGFR (serum profile). Blood samples will be sent to Midlands Pathology for spinning and storage for batch analysis, and stored at −80°C for future analysis.

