Selection bias is a key issue in diagnostic accuracy studies. This bias would occur if GPs enrolled only those patients they believed to have a high probability of heart failure. This would mean more symptomatic or more severe cases would dominate the study sample and result in an over-estimation of the test-accuracy of the CDR [57,58]. In our study, the consecutive inclusion of all symptomatic patients will minimise the risk of introducing this type of bias. GPs will be asked to refer all patients over 55 years of age presenting with the target symptoms regardless of whether or not heart failure is suspected by the doctor and excluding patients with pre-existing confirmed heart failure. Verification bias is also a potential limitation and may occur if patients with low pre-test probability of heart failure were to be excluded from undergoing reference standard diagnostic testing to verify the diagnosis of heart failure. This would result in an over-estimation of test sensitivity [58]. Performing all diagnostic assessments on all patients included in the study will minimise this potential source of bias.

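### As written, eligibility can be settled after the study tests, so entry to the primary accuracy table could depend on results that also inform the reference diagnosis

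*Protocol article*

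**What the plan says.** The Patient eligibility section describes two stages. First, "Patient eligibility will be determined by the GP using information from clinical history and examination". Then, "The eligibility criteria will be confirmed by investigation and specialist interpretation of clinical assessments". The article does not say which investigations are meant, when the confirmation takes place, whether the specialist is blind to the rule, NT-proBNP or echo, or what happens to a patient who is not confirmed.

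A separate check appears in the section on referral to the research clinics. The GP's web form serves as the referral letter, "which we shall check to confirm eligibility and to ensure that the patient has contacted the research assessment team". That is a check of a form by the study team.

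Three exclusion criteria bear on the point:
- "Known pre-existing HF or LVSD of any cause"
- "Obvious clinically determined alternative diagnoses such as chest infection, exacerbation of chronic obstructive pulmonary disease or asthma"
- "Major co-morbidity or other alternative diagnoses of no obvious acute and self-limiting cause"

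The Limitations section relies on consecutive inclusion of every symptomatic patient, whether or not the GP suspects heart failure, as its protection against selection bias.

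**The concern.** In a diagnostic validation study, the patients in the accuracy table should be those to whom the rule would be applied. The Clinical decision rule section places the rule at the start of the pathway, when the GP has no ECG, echo or specialist opinion. If such results can decide who is eligible, the table may lose patients whom the rule would meet in practice.

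The same results also inform the reference diagnosis, so a decision on eligibility could be made by someone who already knows, or nearly knows, which cell of the table the patient will fall in. Basal crepitations alone make a patient rule-positive. A patient with lung disease, crepitations and no heart failure is therefore a plausible false positive, and one whom specialist review might relabel as having an excluded condition. If such patients made up most of those removed, specificity and positive predictive value would look better than they are.

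**Working it through.** **Does the wording reach beyond the form check?** The GP is limited to history and examination, so investigation must mean something further. The Diagnostic assessment section places the ECG, echo, NT-proBNP and creatinine at the research clinic, with a chest x-ray arranged by the GP. The form check at referral involves neither an investigation nor a specialist. The natural reading is therefore that confirmation uses the study tests. By then the GP has recorded the rule's clinical features (Clinical judgment section).

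**Which exclusion leaves room?** The criterion naming chest infection and exacerbations of airways disease is confined to diagnoses that are obvious on clinical grounds, so a condition first seen on a test does not meet it. The major co-morbidity criterion has no such limit. Its examples include malignancy and severe respiratory disease, which a chest x-ray or specialist review could bring to light.

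**Inputs (Sample size section).** 500 patients, prevalence 30%, sensitivity 94%, specificity 48%.
- With heart failure: 500 × 0.30 = 150, of whom 150 × 0.94 = 141 are true positives and 9 false negatives.
- Without heart failure: 350, of whom 350 × 0.48 = 168 are true negatives and 182 false positives.

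**The plan's own precision.** Half-width = 1.96 × √(p(1−p)/n).
- Sensitivity: 1.96 × √(0.94 × 0.06/150) = 3.8 points (stated: within 4).
- Specificity: 1.96 × √(0.48 × 0.52/350) = 5.2 points (stated: within 6).

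Both stated figures are reproduced.

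**Effect of removal after testing.** The article gives no removal rate, so every row below the first is an assumption. Specificity = TN/(TN + FP); PPV = TP/(TP + FP).

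| Removed | Specificity | PPV |
|---|---|---|
| Nobody | 168/350 = 48.0% | 141/323 = 43.7% |
| 18 false positives | 168/332 = 50.6% | 141/305 = 46.2% |
| 35 false positives | 168/315 = 53.3% | 141/288 = 49.0% |
| 20% of false positives, 10% of true negatives | 151.2/(151.2 + 145.6) = 50.9% | 141/(141 + 145.6) = 49.2% |
| 35 without heart failure, regardless of rule result (16.8 TN, 18.2 FP) | 151.2/315 = 48.0% | 141/(141 + 163.8) = 46.3% |
| 35 true negatives | 133/315 = 42.2% | 141/323 = 43.7% |

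The 18 and 35 patients are about 5% and 10% of the 350 without heart failure, or about 10% and 19% of the 182 false positives. The second and third rows assume that every removed patient is a false positive, which is the extreme case in that direction. In the fifth row PPV still rises, because removing only patients without heart failure raises prevalence.

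**The case against.** The strongest reply is that nobody is said to be removed. Confirming may mean no more than verifying. The sentence that follows has a specialist panel validate earlier diagnoses and investigations, which fits the rule that a prior heart failure label counts only with objective evidence. The Statistical analysis section classes patients as referred by the rule or remaining, and describes no exclusion after testing. This stands: removal is what the wording permits, not what the article announces.

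A second reply is that a journal article leaves the handling of patients later found ineligible to the full protocol or analysis plan. That would answer a complaint about silence. Here the article states a rule, and the rule as stated ties eligibility to investigations.

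Some stronger readings are tempting but not supported:
- **That removal would selectively drop false positives.** The article does not show this. Lung disease without crepitations, infarction history or oedema, and with a low peptide, is a true negative. Removing patients with known heart failure would bear mainly on sensitivity.
- **That the Limitations section is contradicted where it says** "Performing all diagnostic assessments on all patients included in the study will minimise this potential source of bias". A patient removed after full testing was still fully assessed, so that sentence would remain true. The tension is with the reliance on consecutive inclusion.
- **That the creatinine test is an exclusion step,** because blood is taken "to perform a serum creatinine test to exclude renal dysfunction". This is ordinary usage for ruling out a condition. The exclusion list names renal dialysis, not renal dysfunction.

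**Conclusion.** The point holds as a badly fixed rule. Followed literally, the eligibility section lets membership of the primary 2x2 table depend on tests that also inform the reference standard. The likeliest route is the broad co-morbidity and alternative-diagnosis exclusion, and the result sits poorly with consecutive inclusion of all symptomatic patients.

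The consequence is a possible bias of unknown size and direction. If 35 false positives were removed, the 5.3-point rise in specificity would match the 5.2-point half-width computed from the plan's inputs and approach the stated 6. If removal were unrelated to the rule result, specificity would not move; if 35 true negatives were removed, it would fall by 5.8 points. These figures rest on the planning values and on assumed removal patterns. They do not show that the study's specificity will be inflated.

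**What to change.** Amend the Patient eligibility section to state that:

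1. Eligibility is fixed on information available at the GP consultation, using the form check already described at referral, and blind to the rule result, NT-proBNP and echo. Because the GP form also carries the rule's clinical features, the eligibility fields should be checked separately from them.
2. All patients who give written consent stay in the primary accuracy analysis whatever the study tests show. The exception is a patient shown to have been ineligible at presentation on facts that predate the tests, for example age under 55 or heart failure proven by an earlier echo.
3. Exclusion diagnoses first found by study investigations are reported by rule result and reference diagnosis. Removing those patients is a sensitivity analysis only.

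The cost is a few sentences and one small extra table. Specificity may come out slightly lower than it would with removal after testing. If the sponsor meant only the form check, the amendment removes the ambiguity without changing the study.
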